## Abstract

**Background:**

Unhealthy behaviors of coronary heart disease (CHD) patients are closely related to the occurrence of major heart events, which increases the readmission rate and brings a heavy economic burden to families and society. Therefore, it is necessary for health care workers to take active preventive and therapeutic measures to keep or establish healthy behaviors of patients. Positive psychological intervention has been proved to be effective, but it has not been reported in the field of CHD in China. The purpose of this study is to explore the effects of positive event recording based on positive psychology on the healthy behaviors, readmission rate, and anxiety of patients with CHD, in order to provide new ideas for the development of secondary prevention strategies for CHD.

**Methods:**

This is a prospective, single-center, randomized controlled trial (RCT). The subjects will be enrolled from the Department of Cardiology, the First Affiliated Hospital of Soochow University. There are 80 cases in total; according to the random number table, the subjects are randomly divided into the intervention group (*n* = 40) and the control group (*n* = 40). The patients in the intervention group will receive the intervention of recording positive events once a week for 3 months, while the patients in the control group receive conventional nursing. The primary outcomes will include healthy behaviors, readmission rate, and anxiety, and the secondary outcomes will include psychological capital, subjective well-being, and corresponding clinical laboratory indicators. The protocol was approved by the Medical Ethics Committee of Soochow University (approval no. SUDA20200604H01) and is performed in strict accordance with the Declaration of Helsinki formulated by the World Medical Association. All participants provide written informed consent.

**Discussion:**

This study will verify whether positive event recording based on positive psychology can make patients maintain healthy behaviors, reduce readmission rate, and improve anxiety after PCI. Then, this study will provide new ideas and references for the development of secondary prevention strategies for patients with CHD.

**Trial registration:**

Chinese Clinical Trials Registry 2000034538. Registered on 10 July 2020.

**Supplementary Information:**

The online version contains supplementary material available at 10.1186/s13063-022-06964-9.

## Background

Coronary heart disease (CHD) is an acute myocardial ischemia and hypoxia disease caused by coronary artery stenosis, which is one of the highest mortality diseases in the world [1]. With the increasing incidence rate and mortality of CHD, it has resulted in a large amount of medical expenses, making coronary heart disease one of the main reasons for the economic burden of chronic non-communicable diseases in China [2, 3]. At present, percutaneous coronary intervention (PCI) has become one of the main methods for treating CHD because of its characteristics such as low trauma, fast recovery, and short hospitalization time. Although PCI significantly reduces the symptoms of CHD, reduces mortality, and significantly improves the quality of life [4], there is still a risk of major adverse cardiovascular events (MACE) in some patients, which can seriously affect prognosis and increase readmission rates [5, 6].

The prognosis of patients with CHD is determined by various factors. Studies have shown that unhealthy behaviors increased the risk of in-stent restenosis (ISR) and the occurrence of MACE [6, 7]. In addition, negative psychology also affected the prognosis of patients after PCI. Iles-Smith et al. [8] confirmed that anxiety was a predictor of readmission. Frasure-Smith et al. [9] concluded that mood disorders were associated with the occurrence of MACE within 2 years in patients with CHD. However, one study has proved that emotional intervention in elderly patients with heart failure can help them improve heart function, reduce the occurrence of falls, and improve the quality of life [10]. It has also been found that psychological interventions for patients can improve treatment cooperation and can also help patients change their lifestyle and establish healthy behaviors [11–13]. Therefore, patients will benefit most if all known risk factors are controlled.

Positive psychology is a part of psychology, which mainly helps people to form good psychological quality and behavior patterns, focusing on positive subjective experience, positive personality traits, and positive social environment, and fully exploiting the individual’s own strength [14, 15]. At present, positive psychology has been widely used in many fields abroad, such as obstetrics and gynecology, and diabetes. Corno et al. [16] found that positive psychological intervention can help pregnant women reduce anxiety and depression and improve happiness index. Huffman et al. [17] carried out positive psychological intervention on patients with type 2 diabetes and found that it can help patients improve treatment compliance; also, Hoeppner et al. [18] showed that positive psychological intervention can help people quit smoking. However, the development of positive psychology in China is relatively less, mainly in the fields of education, mental illness, etc. The study by Lan et al. [19] clarified that psychological intervention based on positive psychology can help patients maintain a good psychological state, improve depression, and improve self-care ability. Zhu et al. [20] also confirmed that positive psychological intervention can improve the disability acceptance and self-care ability of stroke inpatients.

The application of positive psychology is currently done in a number of different ways, such as expressive writing, mindfulness therapy, gratitude therapy, hope therapy, etc. These methods have a positive effect on reducing negative emotions and improving the subjective well-being of patients. Writing is a unique human behavior of information expression, communication, and creation, and the positive event recording in this study is to express the positive experience or feelings related to the individual through writing [21], which has also been applied to relevant fields and achieved certain curative effects. For example, an intervention study of 411 participants, conducted by Seligman [22] showed that recording positive events significantly improved the well-being of those who were involved. Burton and King [23] found that recording positive events can help people improve their cognition. Suhr et al. [24] have shown that the benefits of writing positive events to help people with mental illness stabilize their mental health. Chinese scholar Xu et al. [25] found that writing positive events and expressing can effectively improve human immunodeficiency virus (HIV)/acquired immune deficiency syndrome (AIDS) patients’ self-discrimination and negative emotions and improve the self-control level. However, there are few reports about positive events recorded in patients after PCI in China, and most of the positive psychological intervention programs in China have poor repeatability and lack of systematic and targeted intervention programs. In view of the simple operation of positive event recording, the time is short, economical, and convenient, and the effect is remarkable, it is necessary to carry out positive psychological intervention for patients after PCI in China to explore its intervention effect and formulate a more suitable positive psychological intervention program for patients with CHD in China.

The purpose of this study is to explore whether the implementation of positive event recording has an impact on the healthy behaviors, readmission rate, and anxiety of patients after PCI in the theoretical framework of positive psychology, in order to provide a reference for improving the quality of specialized nursing and formulating secondary prevention strategies for patients with CHD.

### Objectives

The general aim of this study is to evaluate the efficacy of positive event recording in patients after PCI.

The primary objective is to explore whether recording positive events will promote or maintain healthy behaviors, reduce readmission rate, and improve anxiety of patients after PCI.

The secondary objective is to explore whether recording positive events can promote the positive emotions, subjective well-being, and clinical laboratory indicators (such as total cholesterol (TC), triglyceride (TG), high-density lipoprotein (HDL), low-density lipoprotein (LDL), height and weight, etc.) of patients after PCI.

## Methods

### Study design and setting

This is a randomized controlled trial, which will be conducted in the Department of Cardiology, the First Affiliated Hospital of Soochow University. A written informed consent will be obtained from each individual by the researcher after the individual has received a sufficient explanation and period of time in which to make a thoughtful decision. All the patients will be randomized 1:1 into the intervention group (*n* = 40) or the control group (*n* = 40). The intervention group is given 3-month positive event recording intervention on the basis of conventional nursing, while the control group received conventional nursing, and both groups will be followed up for 3 months at the end of the intervention. The Cardiovascular Medicine Department of the First Affiliated Hospital of Soochow University is currently the largest cardiovascular disease diagnosis and treatment center in South Jiangsu Province, China. It has 180 beds, four cardiac catheterization rooms with advanced equipment, and a cardiac supersonic room and cardiac function room. Annually, an average of 5000 open-heart surgery candidates and 400 emergency operations are treated in the department. The protocol design is based on the Consolidated Standards of Reporting Trials (CONSORT) guidelines and Standard Protocol Items: Recommendations for Interventional Trials (SPIRIT) checklist (see Additional file 3). Figure 1 presents a schematic flow diagram of the study.

**Fig. 1 Fig1:**
[figure not shown]
Schematic flow diagram of the study

### Participants

#### Inclusion criteria

Participants must meet the following criteria:

Those who are aged 18 years or olderThose who meet the diagnostic criteria of coronary heart disease in the ninth edition of Internal Medicine, including stable angina, unstable angina, myocardial infarction, and acute coronary syndrome [26]Those who are after PCIThose who agree to participate and provide written informed consentThose who have been living in Suzhou for a long time or are not leaving Suzhou for half a yearThose who are clear-headed, normal-thinking, and able to communicate with each other

#### Exclusion criteria

Applicants who meet any of these conditions cannot participate in this study:

Those who have severe cognitive impairment, mental illness, and non-cooperationThose who have other serious diseases that affect survival, such as advanced cancer Those who could not record for 4 consecutive weeksOther reasons determined by the investigators that make participation in the clinical trial inappropriate

#### Withdrawal criteria

Participants who meet the criteria summarized below are withdrawn from the study. The subjects who are withdrawn after randomization will be followed up for outcomes. Reasons for withdrawal will be documented in follow-up records and data will be analyzed using the intention-to-treat (ITT) principle.

All subjects have the right to withdraw for any reasonThose who could not complete the test as required, with serious adverse events and complicationsFailed to have three consecutive telephone connections during the follow-up period at the end of the study

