#### Study schedule

The items to be measured at each visit are listed in Table 1.

**Table 1 Tab1:** Schedule of enrollment, intervention, and assessment

Items	Screening	Post-allocation							3 months after the trial
	Visit 1 (day − 7 to − 2)	Visit 2 (day 0)	Visit 3 (week 1)	Visit 4 (week 2)	Visit 5 (week 3)	Visit 6 (week 4)	Visit 7 (week 8)	Visit 8 (week 12)	Visit 9 (week 24)
Informed consent	X								
Inclusion/exclusion criteria	X								
Randomization		X							
Intervention		X	X	X	X	X	X	X	
Basic information^a^	X								
Body measurement^b^	X	X	X	X	X	X	X	X	X
Vital signs	X	X	X	X	X	X	X	X	X
Medical history^c^	X								
General physical examination	X							X	X
Compliance monitoring				X					
Healthy behaviors	X							X	X
Readmission rate								X	X
Anxiety	X							X	X
Psychological capital	X							X	X
Subjective well-being	X							X	X
Clinical indicators^d^	X							X	X
Adverse event monitoring			X	X	X	X	X	X	X

^a^Age, gender, job, medical insurance, exercise, smoking habit, drinking habit, sleep pattern, etc.

^b^Height and weight, but only weight for visit 2 and follow-up

^c^Including general medical history and family history of CHD

^d^Including TG, TC, LDL, HDL, blood glucose, etc.

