#### Intervention

After randomization, the patients in the control group will receive conventional nursing, and the patients in the intervention group will record positive events for 3 months in addition to conventional nursing, that is, once a week for 12 weeks. Each patient in the intervention group will be assigned a notebook to record positive events and a health education manual. The specific implementation plan is as follows.

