#### Sample size calculation

Calculated according to the formula of sample size estimation based on the comparison of the mean of two independent samples [35]: *n*_1_ = *n*_2_ = 2[(*Z*_*α*_ + *Z*_*β*_)*σ*/*δ*]^2^ + *Z*^2^_α_, *σ* is the standard deviation, *δ* is the difference between the two population means, *n*_1_ and *n*_2_ are the required contents of the two samples, respectively, and *Z*_*α*_ and *Z*_*β*_ are *Z* values corresponding to the type I error probability and the type II error probability, respectively. At bilateral *α* = 0.05, power = 0.8, *Z*_*α*/2, ν_ = 1.96, *Z*_*β, ν*_ = 0.842, *σ* = 12.68, and *δ* = 10.39, the sample size for each group is 25 cases. Considering the 20% sample loss rate and other factors, the total number of samples is expected to be 80.

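### The four-week non-recording item sits among the exclusion criteria but can only be observed after randomisation and in the intervention arm; applied as written, it conflicts with the stated ITT analysis

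*Protocol article*

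**What the plan says.** Four parts of the protocol article bear on this point.

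- **Exclusion criteria.** The list opens with "Applicants who meet any of these conditions cannot participate in this study". One of its items is having been unable to record over four consecutive weeks.
- **Intervention.** Recording belongs to one arm and follows allocation: "After randomization, the patients in the control group will receive conventional nursing", whereas "the patients in the intervention group will record positive events for 3 months in addition to conventional nursing". The programme is weekly for 12 weeks.
- **Study schedule (Table 1).** Eligibility is checked at visit 1 only, on days −7 to −2. Randomisation is at visit 2, day 0. No run-in is described, and no screening procedure concerns recording. Compliance monitoring is marked once, at week 2.
- **Withdrawal criteria.** "The subjects who are withdrawn after randomization will be followed up for outcomes", and "data will be analyzed using the intention-to-treat (ITT) principle". The grounds listed are the patient's right to withdraw, inability to complete as required (in wording tied to serious adverse events and complications), and three failed telephone contacts in a row. The four-week item is not among them.

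**The concern.** An eligibility criterion should be something that can be settled before allocation. This one describes behaviour during the assigned intervention. A control patient has nothing to record, so in practice only intervention patients could meet it.

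If site staff treat it as an exclusion, the analysed intervention arm becomes the patients who kept recording, while the control arm stays whole. Patients who stop recording may well be those with poorer health behaviours or more anxiety. Dropping them would then move HPLP II and SAS in favour of the intervention even if recording had no effect. Staff would know whom the item applies to, because each patient's records are reviewed at the weekly contact. Outcome data not collected from such patients cannot be recovered later.

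**Working it through.** **1. Can the item be met before randomisation?** Four weeks is 28 days. Screening begins at most 7 days before allocation, and recording has not yet started. Actual non-recording over four weeks therefore cannot be observed at visit 1. It can be observed only during the 12-week programme, and only in the intervention arm.

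**2. Do the two sections agree about a randomised patient who stops recording?** Under Exclusion criteria such a patient cannot take part. Under Withdrawal criteria a patient withdrawn after randomisation is followed up and analysed by ITT, but four-week non-recording is not a listed ground. No section says which rule applies.

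**3. The plan's own figures.** The sample size section gives "At bilateral *α* = 0.05, power = 0.8", σ = 12.68, δ = 10.39 and 25 per group. The main term is 2 × (2.802 × 12.68/10.39)² = 23.39, which rounds up to 24. Adding 1.96²/4 gives 24.35, which rounds up to 25 and matches the stated figure. This point does not depend on it. With all 40 per arm analysed, power for that σ and δ is about 96%, so power gives no reason to drop anyone.

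**4. Illustration of the bias if the exclusion were applied.** The article gives neither the share of patients who would meet the item nor how their outcomes differ. Both are assumptions here:

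- f = share of the 40 intervention patients removed: 10%, 20% or 30% (4, 8 or 12 patients)
- D = how much worse the removed patients score than the rest: 0.5 or 1 SD
- no true effect, and 40 controls all kept

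The formulas are:

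- bias = f × D, in SD units
- n₁ = 40(1 − f)
- shift in z = bias / √(1/n₁ + 1/40)
- type I error = P(Z > 1.96 − shift) + P(Z < −1.96 − shift)

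| f | n₁ | √(1/n₁ + 1/40) | D | Bias (SD) | Shift | Type I error |
|---|---|---|---|---|---|---|
| 0.1 | 36 | 0.230 | 0.5 | 0.05 | 0.22 | 5.5% |
| 0.1 | 36 | 0.230 | 1 | 0.10 | 0.44 | 7.2% |
| 0.2 | 32 | 0.237 | 0.5 | 0.10 | 0.42 | 7.1% |
| 0.2 | 32 | 0.237 | 1 | 0.20 | 0.84 | 13.5% |
| 0.3 | 28 | 0.246 | 0.5 | 0.15 | 0.61 | 9.3% |
| 0.3 | 28 | 0.246 | 1 | 0.30 | 1.22 | 23.0% |

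Simulated t-tests (15,000 runs per case) gave 5.3%, 7.2%, 7.3%, 13.7%, 9.4% and 23.2% in the same order.

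On the protocol's σ, the bias is 0.05 × 12.68 = 0.6 to 0.30 × 12.68 = 3.8 points, or 6–37% of δ. The article does not say which scale σ and δ belong to, so the SD units are the safer reading.

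**5. A second model.** Here the least adherent share f is removed, and adherence correlates with outcome at ρ, also assumed. Bias = ρ × φ(z_f)/(1 − f), where φ is the standard normal density and z_f its f-quantile. Type I error comes from 20,000 simulated t-tests per case.

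| f | Bias (SD), ρ = 0.3 to 0.5 | Type I error |
|---|---|---|
| 0.1 | 0.06–0.10 | 5.9–7.0% |
| 0.2 | 0.11–0.18 | 7.1–11.5% |
| 0.3 | 0.15–0.25 | 9.0–17.4% |

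With ρ = 0 the bias is zero and the type I error stays at about 5%.

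**The case against.** The strongest reply is that the exclusion list is addressed to applicants and checked only at visit 1. On that wording the item could mean inability to record as judged at screening, which would apply equally to both future arms. This reading is open but weaker: the item is phrased as something that has happened over a set period, that period fits the weekly programme, and no screening procedure assesses it.

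A second reply is that the only explicit rule for patients who leave after randomisation is follow-up plus ITT. In addition, Compliance monitoring answers poor recording by looking for causes and revising the scheme, and does not mention removing patients. Both observations are correct. The sentence on following up withdrawn patients is sound in itself; the misplaced text is the one item in the exclusion list.

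A reader might infer that poor adherers will be removed and that the comparison is therefore biased. The article does not say so: nowhere does it state that they leave follow-up or analysis, and if the Withdrawal criteria govern, this bias does not arise. A reader might also infer that ITT cannot be delivered because patients are described as withdrawn and yet followed. Withdrawn can be read as stopping the intervention, and a finer split of withdrawal statuses is detail that an article commonly leaves to the full protocol.

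**Conclusion.** The point holds as an internal conflict that needs reconciling. A condition that can be observed only after randomisation, and only in the intervention arm, is listed as an eligibility exclusion. Applied as written, it would undo the ITT commitment made in the next section.

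The harm is conditional on two things: that the exclusion is applied, and that adherence is related to outcome. Given both, the assumed ranges (10–30% removed, deficit 0.5–1 SD, no true effect) give 0.05–0.30 SD of bias and a type I error of about 5–23%. The low end is practically nominal. The correlation model gives the same direction, with a maximum of about 17%.

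These figures apply to HPLP II and SAS only. Readmission is a proportion, and the calculation does not show a shift in it. Nor should the protocol's 20% loss allowance be taken as support for the 20% row: it is a general allowance for losses and other factors, not a forecast of non-recording in one arm.

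**What to change.** Reconcile the Exclusion criteria with the Withdrawal criteria:

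- Take the four-week item out of the exclusion list. Keep it only as a definition of non-adherence, for description or a supplementary analysis.
- State that a randomised patient who stops recording is still followed for HPLP II, SAS and readmission at visits 8 and 9 (weeks 12 and 24) and is analysed in the allocated arm.

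The grounds for stopping the recording itself remain the team's decision.

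The cost is a change of wording in two sections. The one downside is that the estimated effect may be somewhat smaller because non-adherers are kept. The article reports 20 volunteers recruited out of 80, so at that stage the clarification could still reach most of the sample.

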### Randomization

#### Sequence generation

Eligible participants who will provide written consent to take part in the clinical trial will be randomly assigned to an intervention group or a control group with an allocation ratio of 1:1. Random sequencing will be generated by an independent professional statistician using the SPSS 25.0 software to generate 80 random numbers. This statistician will not be involved in this study and only help us generate the random numbers and allocation sequence.

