#### Primary outcome measure

Healthy behavior: The Health Promotion Lifestyle Profile II (HPLP II) will be used to measure patient’s healthy behavior. The scale was revised by American nursing scientist Walker [31], which mainly includes 6 dimensions and 52 items. The total Cronbach’s *α* coefficient of the scale is 0.94, and the Cronbach’s *α* number of each dimension is 0.79–0.87. Each item is scored by grades 1–4; the higher the score, the better the healthful lifestyle. It will be checked at visits 1, 8, and 9.Readmission rate: In this study, readmission is defined as the readmission caused by cardiovascular problems, including hypertension, angina, arrhythmia, cardiac insufficiency, etc., excluding the cases of readmission due to cold, tumor, and other factors. The readmission will be followed up by telephone for 3 months. The readmission information will be collected at visits 8 and 9.Anxiety: The Self-rating Anxiety Scale (SAS) will be used to measure the anxiety of patients with CHD. The scale was compiled by Chinese professor Zung (1971), there are 20 items on the scale, each item is scored by grades 1–4, and items 5, 9, 13, 17, and 19 are scored in reverse. According to the results of Chinese norm model results [32], the cut-off value of the SAS standard score is 50, of which 50–59 is mild anxiety, 60–69 is moderate anxiety, and over 69 is severe anxiety. The scale has been widely used in China and its validity and reliability have been verified (Cronbach’s *α* 0.82). The anxiety score will be measured at visits 1, 8, and 9.

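### No described step balances diagnosis or baseline anxiety, and the stated unadjusted tests leave any chance imbalance between two arms of 40 uncorrected

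*Protocol article*

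**What the plan says.** **Allocation.** Under Sequence generation, patients are "randomly assigned to an intervention group or a control group with an allocation ratio of 1:1", and the method is "Random sequencing will be generated by an independent professional statistician using the SPSS 25.0 software to generate 80 random numbers". The same section says that the statistician will "only help us generate the random numbers and allocation sequence". Study design and setting repeats the ratio ("All the patients will be randomized 1:1 into the intervention group") and gives 40 patients for each arm. The abstract also gives 40 and 40 but names a different source of randomness: "There are 80 cases in total; according to the random number table, the subjects are randomly divided into the intervention group". None of these places describes blocks, strata or minimisation, or says how a number becomes an arm.

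**What is known beforehand.** The inclusion criteria admit a wide range of coronary disease, "including stable angina, unstable angina, myocardial infarction, and acute coronary syndrome". Table 1 puts the eligibility check and the baseline SAS at visit 1 (day −7 to −2), and randomisation at visit 2 (day 0). The Primary outcome measure section also gives an anxiety threshold: "the cut-off value of the SAS standard score is 50".

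**Analysis.** The Statistical analysis section names the two-sample t-test or Mann–Whitney test for measurements and the chi-square or Fisher test for counts. It names no baseline value or other covariate.

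**The concern.** Two of the three primary outcomes have an obvious baseline predictor that is already collected. Anxiety at follow-up should depend on anxiety at visit 1. Cardiovascular readmission plausibly depends on whether the patient came in with stable angina or an acute event. With 40 patients per arm, chance differences in such factors are common. A trial can handle them in the allocation, in the analysis, or in both; as described, this one does neither.

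Readmission is the more exposed outcome, because it has no baseline value of its own from which to compute a change score. Its only protection would be a prognostic factor such as diagnosis, and the stated test does not use one. If the arms happen to differ in case mix, a modest result in either direction will be hard to read. Even when they do not differ, the unadjusted tests give up precision that the visit 1 data could supply.

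**Working it through.** **The plan's own figures.** On this point the plan gives only the arm sizes: 40 + 40 = 80, which agrees with the 80 random numbers. It gives no expected distribution of diagnoses, no proportion with SAS of 50 or more, and no SAS standard deviation. The prevalences below are therefore assumptions, shown as a range.

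**1. Binary factor, 40:40 forced.** Let K of the 80 patients carry the factor and let X be the number of carriers in the intervention arm. With exactly 40 allocated to each arm and no strata,

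P(X = x) = C(K, x) · C(80 − K, 40 − x) / C(80, 40).

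The difference between arms is |x − (K − x)| / 40 = |2x − K| / 40.

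- A difference of 20 points or more means |2x − K| ≥ 8.
- A difference of 15 points or more means |2x − K| ≥ 6.

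| Assumed prevalence | K | P(≥ 15 points) | P(≥ 20 points) |
|---|---|---|---|
| 20% | 16 | 16.1% | 4.8% |
| 30% | 24 | 22.2% | 8.7% |
| 50% | 40 | 26.3% | 11.7% |

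For K = 40, for example, the 20-point event is x ≤ 16 or x ≥ 24.

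**2. Baseline SAS as a continuous score.** In standard deviation units, the difference between two means of 40 has standard error √(2/40) = 0.2236. From the normal distribution:

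- P(|difference| > 0.2 SD): 0.2 / 0.2236 = 0.894, giving 37%.
- P(|difference| > 0.3 SD): 0.3 / 0.2236 = 1.342, giving 18%.
- P(|difference| > 0.5 SD): 0.5 / 0.2236 = 2.236, giving 2.5%.

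This step needs no SAS standard deviation.

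**3. What the stated analysis does with such a gap.** If ρ is the correlation between visit 1 and follow-up SAS, a baseline gap of g SD is expected to carry over as about ρ·g SD. The unadjusted comparison leaves that in the estimate; ANCOVA removes it. ANCOVA also reduces the variance of the treatment estimate to about (1 − ρ²) of the unadjusted variance. The documents give no ρ, so the gain is left as a formula.

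**4. Error rate.** Over all possible randomisations the gap in steps 1 and 2 averages zero, and its spread is already part of the outcome variance used by the t-test. The unadjusted tests therefore keep their 5% level. The loss is in precision and in how far a single result can be trusted.

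**The case against.** The strongest objection is that simple, unstratified randomisation is legitimate in a single-centre trial and keeps the test valid. The document is also a condensed article, so blocking details and the rule that turns numbers into arms may sit in the full protocol. Both points stand. The absence of strata is not an error in itself, and nothing here shows bias. What remains is that the Statistical analysis section does name the tests, and they are unadjusted.

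A reader might go further and infer that the sequence is unrestricted and that the 40:40 split is left to chance. The documents do not support that. Eighty numbers drawn in advance, a separately mentioned allocation sequence and arms fixed at 40 each fit ranking the numbers and assigning 40 to each arm at least as well as independent coin flips. Ranking guarantees 40:40 once all 80 are enrolled. Unequal arms would also cost little. With the plan's SD of 12.68 and difference of 10.39, the noncentrality is 10.39 / (12.68 · √(1/40 + 1/40)) = 3.66 at 40:40 and 10.39 / (12.68 · √(1/31 + 1/49)) = 3.57 at 31:49. The t-test power is 95.1% and 94.1%.

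A reader might also infer an inflated false-positive rate. That holds only if one first assumes that a large imbalance has occurred and persisted to follow-up. It would also need an SD for SAS, and the Sample size calculation does not say which outcome its SD belongs to.

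Finally, the abstract's random number table and the SPSS numbers in the methods differ in wording. That calls for one consistent description but is not evidence of a flawed sequence.

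**Conclusion.** The point holds as a weakness of precision and credibility. As described, balance on diagnosis and visit 1 SAS rests on chance, and the stated comparisons cannot correct an imbalance. With exactly 40 per arm, a 20-point difference in a binary factor arises in 4.8% to 11.7% of such trials across assumed prevalences of 20% to 50%. Baseline SAS differs by more than 0.3 SD in 18%.

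These figures assume a forced 40:40 split and no stratification. They would shrink if the full protocol turned out to stratify on these factors. The case for adjusting the analysis would remain, because the visit 1 data predict the outcome whether or not the arms are balanced. No claim is made that the arm sizes are uncontrolled or that the overall type I error departs from 5%.

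**What to change.** In Statistical analysis:

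- Make the primary comparison of SAS an ANCOVA on the visit 1 score, with diagnosis (stable angina versus the other listed diagnoses) as a covariate.
- Compare readmission with a Mantel–Haenszel test or estimate stratified by the same diagnosis grouping.
- Keep the unadjusted t or Mann–Whitney and chi-square or Fisher tests as sensitivity analyses.

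In the abstract and in Sequence generation, describe one allocation method in the same terms, including how the random numbers become arms and any restriction used.

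Both variables are already collected before randomisation, so the cost is a few sentences in an amendment, made before any outcome data are compared.

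Moving the remaining patients to permuted blocks stratified by diagnosis and SAS is optional. The Trial status section reports 20 of 80 recruited, so about 60 patients would be spread over four strata under a second scheme. With blocks of up to 6, each stratum could end 3 patients apart, so 4 × 3 = 12 overall, or 34:46 at worst. The adjusted analysis does not depend on that change.
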